#### 2.9.2. Secondary Outcome Measures

The secondary outcomes (preliminary efficacy) comprise anthropometric, clinical, and psychological variables selected as of the standard measures for monitoring and prevention of complications in diabetes [44]. These variables will be assessed twice at the intervention, at baseline and after 3 months for HbA1C, blood pressure, body mass index (BMI), weight and waist circumference. Change in outcomes post-intervention will help to determine if the intervention is feasible, acceptable, and effective. Table 3 provides the timeline for the assessment of the variables.

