#### 2.9.5. Predetermined Progression Criteria to Proceed to a Larger Trial

Before the feasibility of RCT started, the research team developed progression criteria. The progression criteria will help to decide on carrying out a full scale based on the findings generated from the feasibility study regarding recruitment, retention, adherence, and overall acceptability [45]. These criteria establish the benchmarks for assessing the trial’s feasibility and determining whether undertake a further larger-scale study. The predetermined progression criteria are presented in Table 4.

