Demographic				
BMI				
Weight				
Blood pressure				
Waist circumference				
HbA1c				
Feasibility Questionnaire				
Summary of Diabetes Self Care Activity (SDSCA), 12-items				
Self-efficacy Scale for Diabetes, 8-items				
Acceptibity Questionnaire				
Likert Scale Satisfaction Questionnaire, 14-items				

**Table 4 ijerph-19-15089-t004:** Health coaching predetermined criteria.

Criteria	Predetermined Cut-Offs
Screening prospective participants	If 60–80% or more of those eligible to participate in the study consented, this supports conducting a large RCT scale trial, but if percentage is less than 50%, there is no significance to move forward.
Recruitment rate	If the recruitment rate of people who were eligible and consented was ≥80% this would support conducting a large RCT trial. If the rate was between 70–65%, this needs further discussion to explore the reasons and whether, if they can be modified, then the trial may progress with cautions. If the rate was ≤65%, there is no significance to moving forward.
Retention rate at 3-months	If the rate was ≥83%, this supports conducting a large RCT scale trial If the rate was less than 83%, there is no significance to moving forward.
Intervention adherence	If the adherence rate was ≥84% of the intervention (≥5 out of the 6 coaching sessions) If the rate was between 84–67% (≥5.4 out of the 6 coaching sessions), this needs further discussion to explore the reasons and whether, if they can be modified, then the trial may progress with cautions. If the adherence rate was less than 67%, there is no significance to moving forward.

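### Table 4's rows can return opposing verdicts on the larger trial and no rule combines them, while section 2.9.2 lets clinical change bear on feasibility

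*Protocol article*

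**What the plan says.** Section 2.9.5 of the protocol article says the team set progression criteria before the study began, describes them as helping the decision, and presents Table 4 as the benchmarks for "determining whether undertake a further larger-scale study". The Abstract also says that the predetermined criteria settle whether a larger trial follows.

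Table 4 has four rows:

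- **Screening.** Favourable: "If 60–80% or more of those eligible to participate in the study consented, this supports conducting a large RCT scale trial". Below 50% is a stop.
- **Recruitment.** Favourable: "If the recruitment rate of people who were eligible and consented was ≥80% this would support conducting a large RCT trial". A band of 65% to 70% calls for discussion. Stop: "If the rate was ≤65%, there is no significance to moving forward".
- **Retention at 3 months.** Favourable: "If the rate was ≥83%, this supports conducting a large RCT scale trial". Stop: "If the rate was less than 83%, there is no significance to moving forward". There is no middle zone.
- **Adherence.** The upper band reads "If the adherence rate was ≥84% of the intervention (≥5 out of the 6 coaching sessions" and ends without a consequence. A middle band calls for discussion, and below 67% is a stop.

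No row refers to another, and section 2.9.5 gives no order of precedence.

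Section 2.9.2, on the secondary outcomes, says: "Change in outcomes post-intervention will help to determine if the intervention is feasible, acceptable, and effective". It gives no threshold and no link to Table 4. Section 2.9.5 bases progression on recruitment, retention, adherence and overall acceptability, with no clinical outcome among them.

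**The concern.** Three rows each speak to the same question, the large RCT, and each can come out either way. Adherence as printed can only caution or stop. When the rows disagree, the article does not say which one governs. Criteria are fixed in advance so that the progression decision is not shaped by the data; without a combination rule, that part of the decision is made once the results are known.

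The sentence in section 2.9.2 is a second, smaller problem. It treats change in clinical outcomes as evidence on whether the intervention is feasible, acceptable and effective. The progression criteria do not use clinical change, and a trial of this size analysed descriptively cannot establish effectiveness.

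**Working it through.** The plan gives no derived figure here, so there is none to reproduce. The check applies the printed cut-offs to results that could occur.

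**Inputs.** 30 participants, 15 per group (section 2.7); cut-offs from Table 4. The number of eligible people and the true rates are not in the document and are assumed below.

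**1. Conflict across rows.** Suppose 30 of 36 eligible people consent.
- 30/36 = 83.3%. Screening (60% or more) and recruitment (80% or more) are both favourable.
- 24 of 30 retained = 80.0%, below 83%: stop.
- 25 of 30 retained = 83.3%: favourable.

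One participant moves the table from agreement to disagreement.

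**2. Conflict between the two consent rows.** Read both as consented divided by eligible. Screening is favourable from 60% and recruitment is a stop up to 65%, so 60% to 65% gets both verdicts. With 30 consenting:
- 47 eligible: 30/47 = 63.8%
- 50 eligible: 30/50 = 60.0%

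Thus 47 to 50 eligible people give opposing verdicts from a single figure. This depends on the shared denominator, which the wording suggests but does not settle.

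**3. How often.** Assume 36 eligible, 30 randomised, 90 coaching sessions (15 × 6), independent rows and one consent draw feeding both consent rows. The chance of at least one favourable and one stop verdict was simulated. Beside it is the exact binomial chance that retention alone is a stop, P(X ≤ 24) with X ~ Bin(30, p).

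| Assumed true consent / retention / adherence | Opposing verdicts | Retention stop alone |
|---|---|---|
| 85 / 85 / 85% | 29% | 0.289 |
| 80 / 80 / 80% | 58% | 0.572 |
| 85 / 80 / 90% | 57% | 0.572 |
| 90 / 90 / 90% | 7% | 0.073 |

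The columns nearly coincide. Screening is almost always favourable, so nearly every retention stop registers as a conflict. If the retention stop were set, purely for illustration, at below 70%, the four figures fall to about 1%, 8%, 6% and 0%. None of these results needs a favourable verdict for adherence of 84% or more, which the table does not state.

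**4. Clinical change.** With 15 per group, the half-width of a 95% interval for an unadjusted difference in means, in standard deviation units, is t(28) × √(1/15 + 1/15) = 2.048 × 0.365 = 0.75. An interval of ±0.75 SD cannot show whether the intervention works. Section 3.1 plans only descriptive summaries and correlations with the number of sessions.

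**The case against.** The strongest reply is that the phrases are not symmetric. A favourable row only lends support, whereas an unfavourable row reads as a block. Support from consent and a block from retention can both be true, and the natural reading is that any stop prevents progression. This largely stands, so a reader who infers that one data set orders the team both to proceed and not to proceed goes too far. But the rule is not written, and describing the criteria as helping the decision leaves room for a different reading.

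A second reply is that the conflict probabilities measure one strict retention cut-off, not a general failure of the table. That is correct, as step 3 shows.

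A third is that section 2.9.2 concerns the intervention, not progression. That also stands. A reader might infer that a good or poor HbA1c change would be used to tip a divided result. No passage says so, and section 2.9.5 lists no clinical outcome. What remains is that feasibility is tied to clinical change in one section and not in the other.

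Finally, the criteria are guidance with a discussion route, and a fuller protocol might hold a combination rule. The discussion route exists only in the recruitment and adherence rows. Section 2.9.5 offers Table 4 as the criteria themselves, and the point is how the printed rows behave, not a missing detail.

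**Conclusion.** The point holds as a weakness in the decision rule that should be corrected. The screening, recruitment and retention rows can return opposing verdicts on the large RCT from ordinary results, and nothing fixes in advance how they combine. The example of 30/36 consenting with 24/30 retained needs no assumption about true rates. The 60% to 65% overlap needs both consent rows to share a denominator.

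The probabilities (about 29% at 85% true retention, 57% at 80%, 7% at 90%) rest on assumed rates and come almost entirely from the 83% retention cut-off. They should not be read as the frequency of conflict once that row is revised.

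The sentence in section 2.9.2 is a separate inconsistency. It gives clinical change a role in judging feasibility that section 2.9.5 and Table 4 do not, and claims a bearing on effectiveness that 15 per group cannot support.

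**What to change.** 1. In section 2.9.5 or under Table 4, state that the least favourable row governs. Proceed only if every row is in its go zone; do not proceed in the present form if any row is in its stop zone; otherwise use the further-discussion route the table already has. For this to work, the adherence row needs a written consequence for its upper band.
2. Reconcile the screening and recruitment rows: give each its numerator and denominator. If they are the same quantity, merge them under one set of cut-offs.
3. Reword section 2.9.2 so that changes in clinical outcomes are exploratory and do not enter the feasibility or progression decision.

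The cost is a few sentences, with no change to data collection or sample size. The downside is that an unqualified decision to proceed becomes harder to obtain, chiefly because of the retention row.

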### 2.7. Sample Size

To the best of our knowledge, there was no previous health coaching RCT feasibility study in the field to use as a reference for the sample size. Thus, this study seeks to recruit at least 9% (n = 30) of the sample size required to carry out a full trial [34], with a minimum of 12 participants in each group [35]. Participants will be randomly allocated to either the coaching group (n = 15) or the control group (n = 15).

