#### 2.8.2. Intervention Procedure

Three trained and qualified health coaches will deliver the coaching sessions. They all will receive training on the intervention curriculum (see Table 2). Additionally, they will be monitored by the researchers throughout the period of delivery of the intervention. The intervention consists of 6 sessions that will be delivered biweekly via face-to-face meetings and telephone coaching over a 3-month period. Intervention group participants will be contacted fortnightly and coached using a combination of different methods; in person, by phone, and by smartphone (e.g., secure messaging such as WhatsApp) while the control group participants only receive the usual care for participants with T2DM with includes general lifestyle advice. Face-to-face coaching is only conducted at baseline and in the third month of the intervention for 30–45 min coaching sessions. In addition, 10–15 min telephone coaching will be delivered for the other four sessions (see Figure 1). 

The health coach works as an ally to enable participants to effectively engage in their self-care needs and address potential self-management barriers. They will be provided with different tools, including a patients’ progress tracker, coach notes log and a coaching log to help them run each coaching session. Participants will be given the opportunity to learn and practice significant skills to help them reach target goals through action plans they set for themselves for better self-care [43]. Table 2 illustrates the operationalised protocol and phases of session delivery

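### Table 4's adherence row contradicts itself: 5 of 6 sessions is 83.3%, short of the 84% go line, and the middle band's 5.4 of 6 is 90%, above it

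*Protocol article*

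**What the plan says.** Section 2.9.5 of the protocol article says that progression criteria were set before the feasibility trial began, names adherence among them, and refers to Table 4 for the cut-offs. The adherence row of Table 4 has three bands:

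- Top: "If the adherence rate was ≥84% of the intervention (≥5 out of the 6 coaching sessions").
- Middle: "If the rate was between 84–67% (≥5.4 out of the 6 coaching sessions"), which calls for discussion and cautious progress.
- Bottom: "If the adherence rate was less than 67%, there is no significance to moving forward".

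The top band states no consequence. I read it as support for a larger trial, because the top bands of the other rows say so. I call the three bands go, amber and stop; these labels are mine.

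Section 2.8.2 fixes the number of sessions: "The intervention consists of 6 sessions that will be delivered biweekly". Section 2.7 fixes the arm size: "Participants will be randomly allocated to either the coaching group (n = 15) or the control group (n = 15"). Section 3.1 lists adherence to coaching sessions among the rates to be given as proportions, and also lists the percentage of sessions completed. No part of the article explains 5.4, gives a rounding rule, or says whether the percentage or the bracket governs.

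**The concern.** Each band gives the same cut-off twice, as a percentage and as a count out of six, so the two should convert into each other. They do not. In the go band the count is slightly easier to meet than the percentage. In the amber band the count is harder to meet than the go count, which reverses the order of the bands.

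The progression decision is the main product of this feasibility study, and a predetermined criterion is meant to fix that decision before the data are seen. If one adherence result can be read as two bands, or as none of the bracketed ones, the reading can be chosen afterwards.

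**Working it through.** **Inputs.** Six sessions per participant (section 2.8.2); 15 coached participants (section 2.7); cut-offs of 84% and 67% with brackets of at least 5 and at least 5.4 sessions (Table 4).

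**Can the printed pairs be reproduced?** Percentage = sessions / 6 × 100.

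- 4/6 = 66.67%, which rounds to 67%.
- 5/6 = 83.33%, which rounds to 83%. It becomes 84% only if rounded up.
- 5.4/6 = 90.00%. No rounding brings this into 67–84%.

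**Reverse direction.** Sessions = percentage × 6.

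- 0.84 × 6 = 5.04
- 0.67 × 6 = 4.02

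The amber percentages therefore cover about 4.02 to 5.04 sessions. The amber bracket starts at 5.4, wholly outside that range and above the go bracket of 5.

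**Pooled over the coaching arm.** Planned sessions = 15 × 6 = 90.

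- Go by percentage: 0.84 × 90 = 75.6, so at least 76 sessions.
- Amber by percentage: 0.67 × 90 = 60.3, so 61 to 75 sessions.
- Go bracket, mean of at least 5: 5 × 15 = 75 sessions.
- Amber bracket, mean of at least 5.4: 5.4 × 15 = 81 sessions.

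| Sessions completed of 90 | Mean per participant | Percentage | Band by percentage | Go bracket (≥5) met | Amber bracket (≥5.4) met |
|---|---|---|---|---|---|
| 60 | 4.00 | 66.7% | stop | no | no |
| 61 | 4.07 | 67.8% | amber | no | no |
| 74 | 4.93 | 82.2% | amber | no | no |
| 75 | 5.00 | 83.3% | amber | yes | no |
| 76 | 5.07 | 84.4% | go | yes | no |
| 81 | 5.40 | 90.0% | go | yes | yes |

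The table shows three things. At 75 sessions the count says go and the percentage says amber, and one further session removes the conflict. From 61 to 74 sessions the percentage says amber but neither bracket is met. No total meets both the amber percentage and the amber bracket.

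**Sensitivity to arm size.** At the section 2.7 minimum of 12 per group, planned sessions are 12 × 6 = 72. Then 0.84 × 72 = 60.48, so go by percentage needs 61, while a mean of 5 is 60 sessions. And 0.67 × 72 = 48.24, so 49 to 59 sessions are amber by percentage and meet no bracket. The pattern is the same.

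**The case against.** The best defence is that the row was built on 5/6 and 4/6, that 83.3% and 66.7% were rounded up to 84% and 67%, and that 5.4 is a misprint. This is plausible, and the go mismatch is indeed small: 84 − 83.33 = 0.67 of a percentage point, which matters at a single pooled total. But the article confirms none of it, and no simple repair of the misprint makes the row consistent. If 5.4 should be 4, then 4/6 = 66.7% is amber by count and stop by percentage. If it should be 5 and 4, then 5 sessions is in both go and amber.

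A second defence is that section 2.9.5 presents the criteria as an aid to the decision, and that amber leads to discussion, not to a fixed verdict. That softens the consequence. It does not make the cut-offs agree.

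Some stronger readings are tempting, and the documents do not support them:

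- A reader might infer that the verdict also turns on percentage versus bracket at means of 4.0 or 5.5 sessions. At 4.0 (66.7%) the percentage says stop and no bracket is met. At 5.5 (91.7%) the percentage and the go bracket both say go; meeting the amber bracket too is untidy but does not make them disagree. Nor does the article give an expected adherence, so no result can be called likely.
- A reader might infer that 84% amounts to requiring all six sessions. That holds only if the cut-off is applied to each participant. Section 3.1 points to a percentage of sessions, and pooled, go needs 76 of 90.
- A reader might object that exactly 84% lies in both go and amber. The wording does overlap, but 0.84 × 6n = 5.04n is a whole number only when n is a multiple of 25, so an unrounded 84% cannot occur with 12 to 15 coached participants.
- A reader might say that the adherence statistic is undefined. Section 3.1 gives its general form, and finer detail may lie in the full protocol or analysis plan.

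**Conclusion.** The contradiction is real and lies within one table row, so it cannot be put down to the condensing of a journal article or to an analysis plan that is not shown. The 5.4 figure is the more serious fault: it is 6 percentage points above the go line (90 − 84) while labelled as the band below it. The mismatch between 84% and 5 of 6 is minor in size but changes the band at exactly 75 of 90 sessions. Between 61 and 74 sessions the row gives a percentage band with no matching count.

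These totals assume 15 coached participants, adherence pooled over all planned sessions, and the first line of the row read as go. The mismatch between percentage and count depends on none of these, because it is already present for a single participant. As this is a predetermined progression threshold, it should be corrected before analysis.

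**What to change.** Delete 5.4 and state that one statistic governs: the percentage of planned sessions completed in the coaching arm. Give non-overlapping bands with counts that match. Two options do this for 90 planned sessions:

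| Band | Option A: exact fractions | Option B: keep the percentages, drop the brackets |
|---|---|---|
| Go | ≥5/6 (75 or more) | ≥84% (76 or more) |
| Amber | ≥4/6 to <5/6 (60–74) | ≥67% to <84% (61–75) |
| Stop | <4/6 (59 or fewer) | <67% (60 or fewer) |

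The options differ only at 75 sessions (go under A, amber under B) and at 60 sessions (amber under A, stop under B). Compared with the printed percentages, option A is the more lenient at both points, so this is a choice for the investigators and not merely an arithmetic correction. They should make and record it before analysis. If the coaching arm is not 15, the counts should be recalculated from 6 sessions per participant. The cost is one table row, with no effect on data collection or resources.

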## Data Availability

All data generated or analysed during this study will be included and are available upon reasonable request from the corresponding author.
